### 14.2. Statistical Analysis Methods

1) Demographic information

For demographic information such as age, height, and weight, descriptive statistics (mean, standard deviation, median, minimum, maximum, etc.) or category frequency and ratio are presented according to the characteristics of the data.

2) Safety and Tolerability Analysis

For safety/tolerability analysis, the abnormal findings observed in safety evaluation lists such as the occurrence pattern of adverse events, vital signs and clinical laboratory results are described, and if necessary, each list is compared according to appropriate classification such as dosing group. Medical history and AEs are coded using the MedDRA (ver. 24.0 or later).

3) Pharmacokinetic Analysis

After calculating pharmacokinetic parameters for each subject, descriptive statistics are summarized by appropriate classification such as dosing group.

To evaluate the pharmacokinetic linearity according to the dose increase, the relationship between  $C_{\max}$ , AUC( $AUC_{\inf}$ ,  $AUC_{\text{last}}$ ) and the administered dose is evaluated through regression analysis, and  $C_{\max}$ , AUC corrected for the administered dose are compared between dosing groups through a parametric or non-parametric statistical test. In addition, parameters such as  $T_{\max}$ ,  $t_{1/2}$ , CL/F can be compared between dosing groups through an appropriate method.

Food effect evaluation is performed by calculating the geometric mean ratio (GMR) of the pharmacokinetic parameters ( $C_{\max}$ , AUC) after a high-fat meal to the fasting and its 90% confidence interval (CI).

4) Exploratory Pharmacodynamic Analysis

After calculating exploratory pharmacodynamic parameters for each subject, descriptive statistics are summarized by appropriate classification such as dosing group.

### 14.3. Interim Analysis

No interim analysis is scheduled in this clinical study.

## 15. Ethics of Research

This clinical trial will be conducted ethically and scientifically in accordance with the KGCP and all relevant regulations. In addition, this clinical study will be conducted in accordance with the Declaration of Helsinki, respecting human dignity and rights and not causing any disadvantage to the subject.

## 16. Data Processing and Quality Assurance

### 16.1. Source Documents

Source documents mean all documents, data, and records such as medical records, electrocardiograms, clinical laboratory test results, and drug dispensing records. Data collected during the study period should be recorded in appropriate source data. Data recorded in the screening/registration log should include the subject randomization number, screening date, and reason for dropping out (in case of dropout), and all screened subjects should be recorded in this log. Access to source data is permitted during clinical study monitoring, inspection, IRB review, and fact-finding by the permitting authority.

### 16.2. Case Report Forms

If eCRF is not recorded until end of clinical study, the appropriate reason should be recorded. All eCRF have remote data collection based on source documents. Sponsor should monitor eCRF periodically and the principal investigator should review the completion and accuracy of the eCRF before writing electronic signature. Data will be frozen after monitoring and completion of principal investigator signature. Thereafter, data validation is performed using an appropriate computer program (SAS, etc.) to verify whether there are logical errors, missing values, or outliers in the eCRF. For all errors found, it is judged whether it is a query, and a query is issued to the clinical trial institution, and the eCRF is revised after the institution confirms the original data. Source documents and eCRF should be kept after verified all data for IRB or relevant government agencies. In addition, investigator should present normal range or references in eCRF to identify and verify the computerized record before clinical study initiation.

### 16.3. Data Entry Process

eCRF will be used in this study. All information recoded in the eCRF is based on subject's source documents and completed the eCRF of all subjects who signed the consent form. The data of eCRF is input through the database system developed using CRScube, and the data input process is performed according to the SOP of the clinical trial institution. Since complete pharmacokinetic data are created after eCRF input is completed, pharmacokinetic data are excluded from the database system entry. After reviewing the completeness and accuracy of the eCRF, the principal investigator digitally signs it.

### 16.4. Storage of Study Documents

In accordance with the KGCP, clinical study-related documents have to be retained for 3 years from the date of product approval or 3 years from the date of completion of the study. The retention period may be extended if the Minister of Food and Drug Safety instructs to do so or if the sponsor determines that it is necessary.

### 16.5. Data Security

All documents, including source documents and eCRF obtained during the clinical study, have to be retained securely, and it should be stored in a locked laboratory (such as a nurse station in a clinical trial center or an investigator's office). The investigator shall not disclose any of the information without consent from the sponsor. Since anonymity of subjects has to be guaranteed, all documents shall use subject numbers and initials instead of names of subjects. Any documents that may identify subjects shall be retained securely by the investigator. If clinical information collected for the purpose of this study is provided to a third party or registered in an open database, information from those who have agreed will be provided, and will be provided as anonymously.

### 16.6. Confidentiality and Publication of Study Results

Since all information obtained from the clinical study is the exclusive intellectual property of the sponsor, the investigator or anyone else involved must strictly maintain confidentiality. Investigators may publish information or data related to this study after consultation with the sponsor.

## **17. Other Considerations Required for Conduct of Safe and Scientific Clinical Study**

### **17.1. Institutional Review Board (IRB)**

Before starting the clinical study, the investigator must be reviewed by IRB about the investigator's brochure, clinical trial protocol, subject informed consent form, method of recruiting subjects (including the Internet homepage (<http://ctcr.snuh.org>), etc.), and other various information provided to the subject in the form of documents. The IRB communicates the results of its review on study implementation to the sponsor and investigator in writing before the initiation of the clinical study. The principal investigator should conduct the clinical study after obtaining the IRB's approval for the clinical trial protocol and amendments. In addition, events that may affect patient safety or the continuous performance of the clinical study, including serious adverse events, in particular safety-related changes, must be reported to the IRB. In accordance with the relevant IRB standards, if necessary, a report on the progress should be submitted to the IRB, and the IRB should be notified at the end of the clinical study.

### **17.2. Clinical Study Institution**

The clinical study institution shall be fully equipped with facilities and specialized personnel required to conduct the clinical study and be fully prepared to conduct this clinical study properly.

### **17.3. Informed Consent Procedures**

The investigator explains to the subject (or his/her representative) participating in the clinical study using pure Korean (native language) so that they can easily understand the nature, scope, and expected result of the study in advance. However, in the case of Caucasians, explanations are made using language that the subject can easily understand. The investigator confirms that the subject clearly understands that he or she can decide to participate in the clinical study at his or her own will, and that he or she can refuse to participate in the clinical study or stop it at any time during the study period without any loss or loss of benefit. After hearing the explanation about the clinical study, the subject has enough time to consider participating in this clinical study, and can sufficiently discuss with family or acquaintances. In addition, if the subject does not understand the clinical study, he or she can ask the investigator for explanation at any time and should be able to receive a satisfactory answer. The investigator must obtain the subject's consent in writing, and the subject's consent form must be signed and dated by the investigator and subject in his/her own handwriting. Among the elderly subjects, if necessary, consent capacity evaluation (e.g., the mini-mental state examination (MMSE) or the Korean Version CSS (Capacity-to-Consent Screen), etc.) can be performed by the researcher. If it is determined that the consent capacity is incomplete, written consent may be obtained from the agent. The original signed consent form is kept by the investigator, and a copy of the signed consent form and an information sheet must be given to the subject (or his/her representative). Investigator should not conduct any tests for the purpose of clinical study before obtaining consent from the subjects. By signing the consent form, the subject consents to the collection and use of the subject's personal information in relation to the participation in the clinical study. Subject's personal information is used for the purpose of identifying the subject's identity and linking it with the clinical information collected during the clinical study process. And collected personal information is not directly used as clinical study data by encoding it so that the identity of the individual cannot be identified. The scope of personal information collected in relation with clinical study includes personally identifiable information (name, contact information, etc.), demographic information, medical records (past medical history, treatment history, etc.) and test results performed in relation with clinical study. All collected data is handled in accordance with laws, rules and regulations on the protection of personal information.

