## 9.2. Inclusion Criteria/Exclusion Criteria

### 9.2.1. Inclusion Criteria

- 1) Young subjects: Healthy Korean or Caucasian volunteers between 19 and 45 years of age at the screening visit

Elderly subjects: Healthy Korean volunteers over 65 years and under 85 years of age at the screening visit

※ Caucasian who were born in Europe, have lived outside Europe for less than 10 years, and both parents and grandparents were of European origin.

- 2) Women: Except for surgical infertility (bilateral fallopian tube occlusion, hysterectomy, bilateral salpingectomy, bilateral oophorectomy, etc.), those who tested negative in the urine pregnancy test (hCG) performed at screening
- 3) Subjects with body weight between 55.0 kg and 90.0 kg and Body Mass Index (BMI) between 18.0 kg/m^2 and 30.0 kg/m^2 at the screening visit

※ Body Mass Index = body weight(kg)/ [height(m)]

- 4) Subjects who completely understand the nature of study and make a voluntary decision to participate in this clinical study and provide the informed consent.

- 5) Subjects who are considered to be suitable to participate in this study based on physical examination, clinical laboratory test results and medical history

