#### 9.2.2. Exclusion Criteria

- 1) Subjects with a clinical evidence or history of hepatic, renal, neurologic, immunologic, respiratory, endocrine, hematologic, oncologic, cardiovascular, psychiatric disease (mood disorders, obsessive-compulsive disorder, etc.) (However, in the case of an elderly person with a history of mild disease, participation is possible if the researcher determines that the drug can be discontinued at least 2 weeks before the expected first dose or 5 times or more before the half-life.)
- 2) Subjects with a history of gastrointestinal disease (e.g., gastrointestinal ulcers, gastritis, stomach cramp, gastroesophageal reflux disease, Crohn's disease, etc.) or surgery (except for simple appendectomy or herniotomy), which can influence the safety and pharmacokinetic evaluation of investigational drugs
- 3) For all women of childbearing age, except for surgical infertility, those who are pregnant, may be pregnant, or are lactating
- 4) Subjects with clinically significant abnormalities in the neurological examination performed at the screening visit
- 5) Subjects with any of the following vital signs at the screening visit
  - ✓ Systolic blood pressure (SBP):  $< 90$  mmHg or  $> 140$  mmHg
  - ✓ Diastolic blood pressure (DBP):  $< 50$  mmHg or  $> 90$  mmHg
  - ✓ Heart rate:  $< 50$  bpm or  $> 90$  bpm
- 6) Subjects with any of the following clinical laboratory test results at the screening visit
  - ✓ AST, ALT:  $> \text{upper normal limit} \times 1.5$
  - ✓ Total bilirubin:  $> \text{upper normal limit} \times 1.5$
  - ✓ CPK:  $> \text{upper normal limit} \times 1.5$
  - ✓ Creatinine clearance calculated by CKD-EPI equation:  $< 60$  mL/min/1.73m^2
  - ✓ Subjects with a positive result in the serology test (syphilis test, Hepatitis B surface antigen, Hepatitis C antibody, Human immunodeficiency virus(HIV) antibody)
- 7) Subjects with any of the following ECG results at the screening visit
  - ✓ PR  $> 210$  msec
  - ✓ QRS complex  $> 120$  msec
  - ✓ QTcB  $> 450$  msec
  - ✓ Other, clinically significant arrhythmias
- 8) Subjects with a history of hypersensitivities including drug allergies (caused by aspirin, antibiotics, etc.), or a history of clinically significant hypersensitivities
- 9) Subjects with a history of alcohol or drug abuse, or with positive reaction to any drug of concern for abuse/misuse at the urine drug screening test

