### 9.3. Withdrawal Criteria

'Enrollment' means that the subject who participated in the study (ie, signed the informed consent form) met the inclusion/exclusion criteria and was assigned a subject randomization number according to randomization. 'Dropout' means that an enrolled subject does not complete the study. Dropout could be decided at any time during the study period for the following reasons. Dropouts of enrolled subjects from the study should be reported on the eCRF with the date of the dropout, date of the last study drug administration and the reason for the dropout.

- 1) When it is judged that it is difficult for the subject to participate in a clinical study any longer due to a clinically unacceptable serious adverse event or abnormality such as a clinical laboratory test value
- 2) When the subject takes any medication that is expected to influence the safety and pharmacokinetic characteristics of investigational drug without the permission of the investigator
- 3) When the major protocol deviation significant enough to consider discontinuation of the study is identified during the study, such as the subject was found not to be eligible based on inclusion/exclusion criteria after enrollment.

- 4) When the subject does not wish to proceed with investigational drug administration or withdraws consent during the study period
- 5) When the subject does not visit on time and cannot be contacted
- 6) In the cases where the principal investigator or sub-investigator decides to withdraw the subject from the clinical study for other reasons

Those who drop out after administering the investigational drug visit the clinical study institution within 7 days if possible of the dropout (or the first recognition of dropout) and conduct an equivalent post-study visit. However, if the subject refuses to visit, if possible, concomitant medications and lists related to adverse events should be checked by phone. Also, if the dropped out subject has clinically significant abnormal test results, follow-up should be continued. Subjects who have been dropped out due to adverse events or deviations of safety standards should be followed up until symptoms subside and abnormal laboratory test values return to standard values, or there is a satisfactory explanation for the observed changes. If follow-up is not possible, it is considered as 'failed to follow up'.

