**MMSE scoring**

24-30: no cognitive impairment

18-23: mild cognitive impairment

0-17: severe cognitive impairment

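### Section 17.3 allows an agent to consent for an elderly volunteer with incomplete capacity, which contradicts inclusion criterion 4 and leaves open enrolling an ineligible person

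*Protocol*

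**What the plan says.** Four parts of the protocol bear on this.

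- **Inclusion criterion 4** (section 9.2.1, repeated in the synopsis) admits "Subjects who completely understand the nature of study and make a voluntary decision to participate in this clinical study and provide the informed consent". It applies to young and elderly alike.
- **Inclusion criterion 1** defines the older group as "Elderly subjects: Healthy Korean volunteers over 65 years and under 85 years of age at the screening visit".
- **Section 9.3** defines an enrolled subject as one who, having signed the consent form, "met the inclusion/exclusion criteria and was assigned a subject randomization number according to randomization".
- **Section 17.3** covers consent. It first requires that "the subject's consent form must be signed and dated by the investigator and subject in his/her own handwriting". It then provides for an assessment ("Among the elderly subjects, if necessary, consent capacity evaluation"), with the MMSE and a capacity-to-consent screen as examples. It continues: "If it is determined that the consent capacity is incomplete, written consent may be obtained from the agent". It also mentions the subject's representative twice, once as someone who may receive the explanation and once as someone who may receive the copies.

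The capacity assessment is not in the screening list of section 10.7.1, and no criterion in 9.2.1 or 9.2.2 uses its result. Appendix 3 prints MMSE score bands, among them "18-23: mild cognitive impairment", without linking any band to capacity or eligibility. Appendix 4 lists the questions of the capacity screen and gives no threshold.

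**The concern.** Criterion 4 is about the volunteer's own understanding and decision, and an agent's signature supplies neither. If the investigator concludes that capacity is incomplete, criterion 4 points to a screen failure, while 17.3 points to a different signatory. The protocol does not say which governs.

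Three things are at stake.

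- **Valid consent.** The elderly cohort consists of healthy volunteers who take an investigational drug once daily for 7 days, and the protocol states no direct benefit for them. Calling this non-therapeutic is an inference from the phase 1 healthy-volunteer design, but a fair one. Section 17.3 itself wants the investigator to confirm that the subject understands the right to refuse or stop.
- **The population described.** Safety, tolerability and pharmacokinetics in healthy elderly subjects are a primary objective, and one small cohort provides all the elderly data.
- **Clean eligibility.** Section 9.3 gives ineligibility discovered after enrolment as an example of a major deviation that can lead to dropout. Following 17.3 could therefore produce a deviation under 9.3.

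**Working it through.** The protocol states no power, error rate or effect size on this point, so the check is a comparison of texts followed by a count of who is affected.

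**Step 1: can 17.3 and criterion 4 both be satisfied?** Take an elderly volunteer whose consent capacity has been judged incomplete.

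| Provision | What it requires or allows | Met when an agent consents? |
|---|---|---|
| Inclusion 4 (9.2.1, synopsis) | Full understanding, voluntary decision and consent by the subject | No |
| 17.3, signature rule | Subject signs by hand | Not if the agent signs alone; possibly if both sign |
| 17.3, agent sentence | Agent may give written consent | Yes |
| 9.3, enrolment | Eligibility criteria met | No, because inclusion 4 is not met |

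The agent sentence is the only one satisfied on every reading. Adding the subject's signature to the agent's would settle the conflict inside 17.3. It would not settle the conflict with criterion 4, because a signature from someone judged to have incomplete capacity does not show full understanding.

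**Step 2: does another rule close the gap?**

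- Exclusion 1 bars neurologic and psychiatric disease, but is relaxed for elderly people with a history of mild disease.
- Exclusion 4 bars "Subjects with clinically significant abnormalities in the neurological examination performed at the screening visit". The screening examination is the full one in Appendix 1, which includes mental status. This is the closest safeguard, but it is not a test of consent capacity.
- Inclusion 5 (suitability on examination, laboratory results and history) and exclusion 19 (investigator's judgement) would allow a refusal but do not require one.

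Each could keep such a person out. None states that incomplete consent capacity excludes, and the only consequence the protocol gives for that finding is agent consent.

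**Step 3: who is affected?** Sections 9.1 and 17.3 together confine the provision to multiple-dose cohort 5.

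- Cohort size: 6 active + 2 placebo = 8.
- Share of the planned trial: 8 / 88 = 9.1%.
- Weight of one hypothetical such subject on active drug within the elderly active group: 1 / 6 = 17%.

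The last figure shows the leverage of a single person in a group of six. It is not an estimate of how often this would happen, and the protocol gives no basis for one. Section 14.1 defines the safety population by receipt of drug rather than by eligibility, so a dosed subject would stay in the safety analysis.

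**The case against.** The strongest reply is that 17.3 governs who signs and leaves eligibility to section 9. Its wording is conditional twice over: the assessment is done only if needed, and agent consent is only permitted. Enrolment under 9.3 still requires the criteria to be met, so an agent's signature waives nothing. An investigator who applies criterion 4 strictly, together with exclusions 1, 4 and 19 and inclusion 5, would turn the volunteer away.

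Much of this stands, and it rules out several stronger readings that a reader might infer.

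- **That the plan puts cognitively impaired people into the cohort.** It does not. The provision is permissive, other criteria may exclude them, and incomplete consent capacity is not the same as cognitive impairment.
- **That an MMSE score in the mild band leads to agent consent.** No section equates an MMSE band with incomplete capacity, and the tools are named only as examples.
- **That the agent signs in place of the subject.** Section 17.3 does not say so. The handwriting rule leaves room for two signatures.
- **That sites would act differently.** The procedures name one centre. The risk is one team facing two instructions.
- **That such a subject could not report symptoms or stop.** This is a plausible worry, but the protocol contains nothing that establishes it.

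The reply does not remove the contradiction. If criterion 4 always prevails, the agent sentence can never lead to a valid enrolment and has no function. If the sentence has a function, it admits someone whom criterion 4 excludes.

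**Conclusion.** The contradiction is real and rests on the protocol's text alone. Section 17.3 permits consent by an agent in the circumstance where inclusion criterion 4 cannot be met, and it does not reconcile that permission with its own rule that the subject signs by hand. The consequence is limited: the text leaves open enrolling an ineligible person in the healthy elderly cohort, which is 8 of 88 planned subjects, 6 of them on active drug. How often this would occur is unknown and may be never.

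The conclusion assumes that incomplete consent capacity is incompatible with full understanding and a voluntary decision, which is the natural reading of criterion 4. It does not depend on any MMSE cut-off or on assuming that the other eligibility criteria fail. The two passages should be reconciled before elderly volunteers are screened, because the question is whether someone may be enrolled without valid consent of their own.

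**What to change.** - Remove the agent-consent sentence from section 17.3.
- State in 17.3, in section 9.2 and in the synopsis that a volunteer whose consent capacity is judged incomplete does not meet inclusion criterion 4 and is a screen failure.
- Review the two mentions of a representative in 17.3 and align them where they imply consent by proxy. They concern the explanation and the copies, so they need not all be deleted.

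The capacity assessment would remain optional and without a stated threshold. That is separate from the contradiction, but the same amendment could say where in screening the judgement is recorded.

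The cost is a wording amendment, with approval under section 17.6. The assessment tools are already appended, and the sample size and analysis do not change. The downside is an occasional elderly screen failure while a cohort of 8 is being filled.
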